### Study setting

We selected subjects for our study from four communities in Chongming district of Shanghai, China, who met the inclusion and exclusion criteria. This study was conducted in May 2022 at Xinhua Hospital Chongming Branch. A total of 54 older people met the eligibility criteria and were enrolled in the study. The subjects were stratified by sex and then randomized into one of three groups (18 in each group): VT group, RT group, and control group. The assessments were performed three times: at baseline (0 week), after intervention (12 weeks), and follow-up (24 weeks).

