### Randomization and blinding

The subjects were informed of the purpose of the study and the safety risks that may happen in the study, and if they were willing to participate in the study, informed consent was required to sign before the subjects were screened. A stratified randomization method by sex was performed on the subjects meeting the eligibility criteria for a balanced distribution so that each group will have the same number of males and females. The stratified randomization sampling was performed by a researcher, who did not participate in our experiment, by a computer program (Research Randomizer Form www.randomizer.org). The subjects were then randomized into three groups: VT group, RT group, or control group at a 1:1:1 ratio. The randomized number and group assignments were sent to a researcher, who also did not participate in our study, as an electronic file with encryption to store the experimental information. The therapists for different intervention groups conducted the intervention according to the group assignments. Only the therapists will not be blinded to the group assignments, and other research staff (including the assessors, data managers, and data statisticians) will be blinded to the group assignments.

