### Sample size

In our study, we used G-Power software version 3.1 to calculated the simple size. A previous study showed that lower limb muscle strength can directly reflect the effect of exercise training on sarcopenia (Eckardt, 2016; Floreani et al., 2018). Thus, lower limb muscle strength was used as the primary outcome for the calculation of simple size. A power of 0.80 with an alpha of 0.05 was obtained in the calculation of simple size of each group, and the effect size was 0.48, which was reported in a previous meta-analysis study (Rogan et al., 2015). Our study adopted this effect size for calculating the sample size. We used above parameters in G-Power software and produced the total simple size as 45 subjects (15 subjects per group). Considering that there is a potential 20% drop rate of subjects, the total sample size should be 54 subjects (18 per group) in our study.

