### Statistical analysis

The results in the study took the questionnaire result and five components of the outcome measurements into account. All results were analyzed by IBM SPSS Statistics version 24 (SPSS, Inc., USA) with a statistical significant difference as *p* < 0.05. Continuous variables were represented by mean ± standard deviation or median. The chi-square test was used for categorical variables. For baseline characteristics data of between-group comparisons, we used the one-way analysis of variance (for parametric continuous data) or Kruskal–Wallis tests (for non-parametric continuous data).

The linear mixed model was used to analyze the differences in the outcome variables between the three intervention groups, which change over time following the principle of intention-to-treat. Missing data were assumed at random and then were processed by using the linear mixed model and maximum likelihood method.

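### The 20% drop-out allowance multiplies 45 by 1.2 to get 54; dividing by 0.8 gives 57, so 54 subjects do not keep the 45 that the stated power requires

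*Protocol article*

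**What the plan says.** The Sample size section takes lower limb muscle strength as the primary outcome and reports three inputs to G-Power. Power and alpha are given by "A power of 0.80 with an alpha of 0.05 was obtained in the calculation of simple size of each group", and the effect by "the effect size was 0.48, which was reported in a previous meta-analysis study". The software then "produced the total simple size as 45 subjects (15 subjects per group"). The allowance for attrition follows: "Considering that there is a potential 20% drop rate of subjects, the total sample size should be 54 subjects (18 per group").

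That total was carried into the trial. Under Study setting the article reports that "A total of 54 older people met the eligibility criteria and were enrolled in the study", and that they were "randomized into one of three groups (18 in each group"). The abstract gives the same total. The article offers no other drop-out rate and no other rule for inflating the sample size.

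**The concern.** The 20% is described as a rate of loss among subjects, so it applies to those who enter the trial. It appears instead to have been added to the number who must remain at the end. The two calculations differ, and adding 20% always gives the smaller number.

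The purpose of the allowance is to have at least 45 subjects left at the planned loss. If 54 does not do this, the sample-size justification for the primary outcome fails at the very drop-out rate it assumes. The base figure has no slack to absorb the gap, because 45 is the smallest total that reaches 80% power under the reading that reproduces it.

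**Working it through.** **Inputs** (protocol article, Sample size, except where noted)

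- Power 0.80, alpha 0.05, effect size 0.48
- Required total before drop-out: 45 (15 per group)
- Drop-out rate: 20%
- Stated total after the allowance: 54 (18 per group)
- Three groups, "VT group, RT group, or control group at a 1:1:1 ratio" (Randomization and blinding)
- Assumption: the article names neither the metric of 0.48 nor the test. I read it as Cohen's f in a one-way ANOVA with three groups and an overall F test.

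**Step 1: reproduce the 45.** With N subjects in k = 3 groups, the noncentrality is λ = N × f² = N × 0.48² = 0.2304 N. Power is the probability that a noncentral F with (2, N − 3) degrees of freedom and noncentrality λ exceeds the 5% critical value of the central F. The smallest N with power of at least 0.80 is 45 (power 0.8005). At 44 the power is 0.790. The stated 45 is matched exactly.

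**Step 2: reproduce the 54.**

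- Adding 20%: 45 × 1.20 = 54 (15 × 1.20 = 18 per group). This matches.
- Dividing by the retained share: 45 / (1 − 0.20) = 56.25, and 15 / 0.80 = 18.75 per group, so 19 per group and 57 in total. This does not match.

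The article's figure therefore comes from the multiplication.

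**Step 3: what 54 delivers.**

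- Remaining after a 20% loss: 54 × 0.80 = 43.2 (18 × 0.80 = 14.4 per group), against 45 (15 per group) required.
- Largest loss that still leaves 45: 1 − 45/54 = 9/54 = 16.7%.
- Shortfall in enrolment: 57 − 54 = 3, one per group.

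**Step 4: power under the reading in step 1.**

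| Subjects remaining | Power |
|---|---|
| 42 (14 per group) | 0.768 |
| 43 | 0.780 |
| 45 (stated requirement) | 0.8005 |
| 54 (no loss) | 0.875 |
| 57 (no loss) | 0.894 |

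**Step 5: does another reading change this?** A group-by-time interaction with f = 0.24, two time points and an assumed correlation of 0.5 also gives 45. Its noncentrality is N × 0.24² × 2 / (1 − 0.5) = 0.2304 N, the same as in step 1, with the same degrees of freedom. The power figures are therefore identical. The head counts in steps 2 and 3 take 45 as given and depend on no reading at all.

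**Step 6: how often 54 would fall short.** If each of 54 subjects independently had a 20% chance of dropping out (my assumption), the probability of at least 45 remaining is 0.34. At the planned rate, falling below 45 is about twice as likely as not (0.66 against 0.34).

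**The case against.** The arithmetic is hard to contest. The case on the other side is about how much it matters.

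**The mixed model uses incomplete data.** The Statistical analysis section says: "Missing data were assumed at random and then were processed by using the linear mixed model and maximum likelihood method". A subject who leaves after week 12 still contributes a week-12 value, so counting only 43 subjects is pessimistic for the 12-week comparison. This stands as a qualification. It does not rescue the allowance: outcomes are measured only at weeks 0, 12 and 24, and someone lost before week 12 supplies a baseline value alone, which adds little to a comparison of change. If incomplete data cost nothing, no allowance would have been needed.

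**The power figures rest on an inferred metric.** This also stands. The article does not say that 0.48 is Cohen's f. Had it been a standardised difference between two groups, power for one pairwise comparison would be about 0.25 with 15 per group and 0.23 with 14. The loss would again be a point or two, and the 45 itself would be the larger problem. That is a separate question. Any power figure put into the text should name its test and metric.

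**The effect is small and recruitment is over.** Two points of power is well within the uncertainty of an effect size borrowed from a meta-analysis, and nothing in conduct or analysis changes. That limits the weight of the point but does not make the sentence correct.

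**The article never says outright that 54 preserves 80% power at 20% loss.** True, but an allowance added directly after a power calculation has no other evident purpose.

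**Conclusion.** The concern holds. On the article's own figures, 54 subjects do not retain the required 45 at the stated 20% drop-out rate. The allowance covers 16.7%, and the total is 3 short of the 57 that three equal groups would need.

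That part rests only on the printed 45, 20% and 54. The power consequence, about 0.78 with 43 remaining or 0.77 with 14 per group, rests on reading 0.48 as Cohen's f in a one-way ANOVA and on subjects who drop out contributing nothing. To the extent that the mixed model recovers information from partial data, the loss at week 12 is smaller. The error is modest in size, but it sits in the justification for the primary outcome and should be corrected.

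**What to change.** Recruitment ended in February 2022 (Trial status) with 54 enrolled, so the remedy is to correct the statement and leave the number as it is. Replace the attrition sentence in the Sample size section with wording such as:

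> With 54 subjects randomised (18 per group), the required 45 remain if drop-out is at most 16.7%. At 20% drop-out about 43 remain, and power is about 0.78 (one-way ANOVA, three groups, Cohen's f = 0.48, alpha 0.05).

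The sponsor should first confirm that the bracketed test and metric are those entered in G-Power. If they are not, the power figure should be recomputed for the test that was used; the 16.7% and the 43 stay as they are.

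The cost is one sentence and a slightly less favourable statement of power. It requires no change to enrolment, conduct or analysis.

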### Statistical analysis

The results in the study took the questionnaire result and five components of the outcome measurements into account. All results were analyzed by IBM SPSS Statistics version 24 (SPSS, Inc., USA) with a statistical significant difference as *p* < 0.05. Continuous variables were represented by mean ± standard deviation or median. The chi-square test was used for categorical variables. For baseline characteristics data of between-group comparisons, we used the one-way analysis of variance (for parametric continuous data) or Kruskal–Wallis tests (for non-parametric continuous data).

The linear mixed model was used to analyze the differences in the outcome variables between the three intervention groups, which change over time following the principle of intention-to-treat. Missing data were assumed at random and then were processed by using the linear mixed model and maximum likelihood method.

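### The mixed model states neither the sex stratification factor nor how baseline is used, and it names maximum likelihood; settling all three costs nothing and brings a modest gain in precision

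*Protocol article*

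**What the plan says.** All references are to the protocol article.

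- **Randomization and blinding:** "A stratified randomization method by sex was performed on the subjects meeting the eligibility criteria", with the aim of equal sex composition in the three arms.
- **Outcome measurements:** every outcome is measured at weeks 0, 12 and 24. The primary outcome is estimated 1RM knee-extension strength in kilograms.
- **Statistical analysis:** "The linear mixed model was used to analyze the differences in the outcome variables between the three intervention groups, which change over time", under intention to treat. Missing data are assumed missing at random and "processed by using the linear mixed model and maximum likelihood method".

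The section gives no list of fixed effects. Sex is not mentioned, and baseline appears only in the between-group tests of baseline characteristics. The text does not say whether the primary test is a group difference at week 12, an overall group effect or a group-by-time interaction.

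**The concern.** Three choices affect the precision and calibration of the primary comparison in a trial with 18 participants per arm.

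- **Sex.** When allocation is balanced on a prognostic factor that the model omits, the model-based standard error of a between-group comparison is too large and the test is conservative. Strength in kilograms plausibly differs by sex: the article sets sex-specific starting loads for the knee-extension test and sex-specific eligibility cut-offs for grip strength and muscle mass.
- **Baseline.** A contrast in change that lets the arms differ freely at baseline is valid. It is less efficient than one that uses the baseline value as a covariate or holds the baseline means equal, as randomisation justifies.
- **Estimator.** Full maximum likelihood does not allow for the fixed effects when it estimates variances. In small samples its standard errors are therefore too small.

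At stake is precision that the trial could have without collecting anything more, together with a slight excess of false positives if maximum likelihood is the estimator.

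**Working it through.** **Plan's own figure.** The article gives no figure for this point. The nearest is the sample size: "A power of 0.80 with an alpha of 0.05 was obtained", "the effect size was 0.48, which was reported in a previous meta-analysis study", which "produced the total simple size as 45 subjects (15 subjects per group"). A one-way ANOVA F test with three groups and Cohen's f = 0.48 (noncentrality 45 × 0.48²) has power 0.8005 at N = 45, so 45 reproduces. A repeated-measures interaction with f = 0.24, two visits and correlation 0.5 is algebraically the same test and also gives 45. The sample size therefore does not reveal which contrast is meant. I use N = 45 (evaluable) and N = 54 (enrolled) below.

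**Assumed inputs.** The article gives neither the correlation r between baseline and week 12 nor the size of the sex difference s (in within-sex SDs). I show ranges. Half of each arm is taken to be male.

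**1. Baseline adjustment.** For outcome variance σ², the change score has variance 2σ²(1 − r) and the baseline-adjusted outcome has σ²(1 − r²). The ratio of standard errors is √[2(1 − r)/(1 − r²)]:

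- r = 0.3: √(1.40/0.91) = 1.24
- r = 0.5: √(1.00/0.75) = 1.15
- r = 0.7: √(0.60/0.51) = 1.08
- r = 0.8: √(0.40/0.36) = 1.05
- r = 0.9: √(0.20/0.19) = 1.03

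The unadjusted standard error is thus 24%, 15%, 8%, 5% or 3% larger.

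**2. Sex in a change contrast.** A constant sex effect cancels within each participant. A mixed-model simulation (18 per arm, three visits, 20% dropout, r = 0.7, 400 replicates, REML) gave these standard errors for the week-12 group-by-time contrast:

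- s = 1: 0.2700 without sex, 0.2695 with sex
- s = 2: 0.2720 without sex, 0.2707 with sex

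**3. Sex once baseline is adjusted for.** Simulated standard errors with 18 per arm and s = 2, the top of the range considered:

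- r = 0.5: change 0.3310; baseline-adjusted 0.3121; baseline and sex 0.2898. Adding sex gives 0.2898/0.3121 = 0.93, a 7% reduction.
- r = 0.8: change 0.2097; baseline-adjusted 0.2055; baseline and sex 0.2006. Adding sex gives 0.2006/0.2055 = 0.98, a 2% reduction.

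With both terms, the gain over the change contrast is 0.3310/0.2898 = 1.14 and 0.2097/0.2006 = 1.05. This agrees with step 1, less a small cost for estimating the baseline slope.

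**4. Sex in a raw comparison at one visit.** Omitting sex adds s²/4 to the residual variance, so the model standard error is inflated by √(1 + s²/4). The actual type I error at nominal 5% is 2[1 − Φ(1.96 × inflation)]:

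- s = 0.5: inflation 1.03, type I error 4.3%
- s = 1: inflation 1.12, type I error 2.8%
- s = 2: inflation 1.41, type I error 0.6%

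**5. Maximum likelihood against REML.** With three group means the ratio of standard errors is √[(N − 3)/N]:

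- N = 54: √(51/54) = 0.972, which is 2.8% too small. Type I error is 5.7% with a t reference and 6.2% with a normal reference.
- N = 45: √(42/45) = 0.966, which is 3.4% too small. Type I error is 5.8% and 6.5%.

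The mixed-model simulation agrees on the standard error: 0.2611/0.2700 = 0.967 at s = 1. Its rejection rates under maximum likelihood (5.0% and 3.7%) have a Monte Carlo error of about √(0.05 × 0.95/400) = 1.1 percentage points, too coarse to confirm or refute the analytic type I error. The simulation in step 3 gave 5.7% to 5.8% (t) and 6.3% to 6.4% (normal) for the change contrast under maximum likelihood, against 5.0% to 5.1% under REML.

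**The case against.** The strongest objection is that silence is not exclusion. The section writes out no fixed effects at all, not even group and time, and an article commonly leaves the covariate list to the analysis plan. Baseline is one of the three measured time points and may already enter the model as a response. Preferring a baseline-adjusted model to a valid change contrast is a matter of efficiency and corrects no error. This stands: the article cannot be said to omit sex or baseline from the model. What remains is that the stated analysis does not carry the stratification factor forward, and that a better model is available from data already collected.

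On the estimator, the phrase about maximum likelihood occurs only in the sentence on missing data. It may mean no more than likelihood-based handling under missing at random, which REML also provides. That too stands, so the 3% figure is conditional.

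A reader might infer something stronger: that ignoring sex greatly inflates the primary standard error and costs much of the trial's power. The documents do not support this. It needs a raw comparison at week 12, whereas the section speaks of group differences that change over time, and a constant sex effect cancels in such a contrast. It also needs a sex difference of about 2 SD. To get that from the starting loads (64% and 45% of body mass), one must assume body masses and an SD that the article does not give. One must also treat initial test weights as measured strength, although the test raises the weight when a participant manages it.

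**Conclusion.** The point holds as a modest improvement at no cost; it is not a demonstrated error. Its main part is baseline. If the model is an unconstrained group-by-time model, the week-12 standard error is about 3% to 24% larger than it need be for correlations from 0.9 down to 0.3; the direction is the same for any correlation below 1. Sex alone makes almost no difference to a change contrast. It brings a further reduction of at most about 2% to 7% once baseline is adjusted for, in the settings examined with a 2-SD sex difference. It would matter more, and in the conservative direction, only for a raw comparison at a visit. Maximum likelihood, if it is the estimator, works the other way: standard errors about 3% too small and type I error of roughly 5.7% to 6.5%. Since these effects differ in direction and depend on readings that the article leaves open, no single net bias in the error bars can be claimed. All sizes rest on assumed correlations and sex differences.

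**What to change.** State the primary analysis along these lines:

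- The primary contrast is the group difference in knee-extension strength at week 12.
- The mixed model has group, time and group-by-time as fixed effects, and sex as a fixed effect because it is the stratification factor.
- Baseline enters either as a covariate, with its interaction with time and weeks 12 and 24 as responses, or as a response with its mean constrained equal across arms. The constrained form also keeps participants who have only a baseline value.
- Estimation is by REML with Satterthwaite degrees of freedom. If the reference to maximum likelihood concerns missing data only, say so.

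If a separate analysis plan already specifies these terms, a sentence in the article or the registry record pointing to it is enough. The cost is wording: sex and baseline are already collected, and the named software can fit the model. It should be settled before group comparisons are seen.

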### Safety monitoring

The occurrence of adverse events during the experiment was recorded. Serious adverse events were reported to the superior unit and recorded, and then the best solution was sought for subjects by researchers. Medical treatments and appropriate medical compensation were provided to the subjects, if necessary. If the subjects thought the next intervention would cause safety problems to them, they had the rights not to continue to participate in the experiment.

### Data management and monitoring

All data in this study were recorded and managed by data management software in Microsoft Excel 365 at baseline (0 week), after intervention (12 weeks), and follow-up (24 weeks), and adverse events and solutions during the experiment were also recorded. In order to ensure the confidentiality of the study, the name of the subjects was not uploaded in the database, but an identifiable number. All researchers used the encrypted computer when recording and saving data to ensure the security of data, with back up data to avoid data loss.

The data monitoring committee (DMC), which is independent of the competing interests and sponsor, regularly monitored and tested the data to ensure the authenticity and reliability of the data. This committee comprises trial experts, clinical experts, investigators, and statisticians.

### Ethics and dissemination

#### Ethics approval

This study was reviewed and approved by the Ethical Review Committee of the Xinhua Hospital Chongming Branch in November 2020 (approval no. CMEC-2020-KT-42) and was registered in the China Clinical Trial Registry on 15 September 2021 (ChiCTR2100051178).

In the study, researchers collected demographic data (including name, age, gender, marital status, occupation, lifestyles, usual physical activity, drug use, and disease history), all questionnaire results, outcome results, and signed informed consent from the subjects. The electronic data were stored in an encrypted computer, and the paper data were be stored in the project office of Xinhua Hospital Chongming Branch.

#### Dissemination

We will authorize the publication of our study in peer-reviewed journals, and also will be performed at domestic or international academic congresses. The individual results will be reported to the subjects of this study by the researcher after publishing. Any changes or additions to the study protocol will be documented at www.chictr.org.cn.

## Discussion

This is the first study comparing the effects of VT and RT in older people with sarcopenia. In addition, we comprehensively discussed the effects of VT and RT on outcomes related to sarcopenia, including anthropometric measurements (BH, BW, and CC), muscle mass (SMM, SMI, ASM, and ASMI), muscle strength (HGS and KES), physical performance (TUG test, GS, and SPPB), blood biomarkers [hs-CRP, TNF-α, IL-6, IGF-1, GH, testosterone, 25(OH)D, MSTN, FST, and CK], and quality of life (SF-36), between two intervention groups and a control group. At the present stage, a sharply increasing proportion of older people are suffering from sarcopenia, causing many adverse outcomes [e.g., falls (Woo and Kim, 2014), fractures (Harris et al., 2017), and other secondary health problems] to older people. Increasing studies have indicated that WBVT is a potential alternative method to delay the progression of sarcopenia in older people, and RT is one of the most effective exercise training methods for sarcopenia in older people. Therefore, we aimed to find an effective, simple training method to prevent and treat sarcopenia.

Our study has the following advantages: First, our study used two training methods (VT and RT) to provide suitable treatment for older people with sarcopenia. However, CRT has the risk of increasing injury like musculoskeletal problems for older people (Keogh and Winwood, 2017). It may be that CRT is too difficult to be implemented for older people, especially for frail older people, which could lead to low participation, low adherence, and perception difficulty (Fisher et al., 2017). The practical application of the research shows that compared with CRT, VT requires less technical abilities, less space, and less time to perform training (Marín and Rhea, 2010). Compared with physically strong older people with sarcopenia, frail older people may be more appropriate for VT, rather than RT. Therefore, we used VT and RT methods for older people with sarcopenia in our study.

Second, our study compared the effects of the two training methods (VT vs. RT) in older people with sarcopenia, rather than focusing on only one training method. For example, previous studies only explored the effects of different protocols of vibration training in older people with sarcopenia (Wei et al., 2016, 2017). A systematic review and meta-analysis by Wu et al. also pointed out that current studies did not explore the efficacy of WBVT compared with other exercise training methods, and recommended more in-depth studies should be carried out in future on the comparison on WBVT with CRT (Wu et al., 2020). Therefore, our study aimed to solve this problem and provide a simple, effective alternative training method for older people with sarcopenia with difficulty to carry out the CRT.

Third, our study selected 20–25 Hz as the relatively appropriate vibration frequency. Previous studies on vibration were limited to comparing the efficacy of different vibration protocols in older people with sarcopenia. Wei et al. found that the most effective frequency of VT to improve muscle performance in older people with sarcopenia ranged between 20 and 40 Hz (Wei et al., 2016, 2017). Daniel et al. also demonstrated that the vibration frequency of about 6–26 Hz can improve GS and decrease the time of the TUG test in frail older people (Wadsworth and Lark, 2020). Stengel et al. found that VT with a frequency of 25–35 Hz produced positive effects on body composition and muscle strength in older people aged ≥ 65 years (von Stengel et al., 2012). Thus, we selected 20–25 Hz as the vibration frequency in our study. In addition, too long vibration exposure time may reduce subjectivity and compliance of older people with sarcopenia during the intervention period (Silva-Grigoletto et al., 2011). Therefore, we adopted a shorter vibration exposure time and increased the number of vibration repetitions.

Fourth, previous studies mostly focused on the acute effect of VT on sarcopenia (Giombini et al., 2013; Perchthaler et al., 2015) and less on the long-term effect of VT on sarcopenia. Thus, our study aimed to explore the long-term effects of VT and RT in older people with sarcopenia. Therefore, we set the intervention period as 3 months, and after intervention for 3 months, we performed the follow-up assessment to explore the remaining effects of VT and RT on sarcopenia in subjects.

Fifth, the subjects of our study are older people with sarcopenia but without other serious diseases. Previous studies mostly focused on young people [such as athletes (Gómez-Bruton et al., 2017; Takanashi et al., 2019; Chang et al., 2021)] and older people suffering from various diseases [such as knee osteoarthritis (Lai et al., 2019; Zhang et al., 2021), Parkinson's disease (Ribot-Ciscar et al., 2017), chronic low-back pain (Kaeding et al., 2017)], or healthy elderly (Camacho-Cardenosa et al., 2019; Jaime et al., 2019; Pérez-Gómez et al., 2020; Cheng et al., 2021). There are relatively few studies on the effects of VT on frail older people (especially for sarcopenia).

Sixth, the indicators measured in our study not only include three primary outcomes of sarcopenia (i.e., muscle mass, muscle strength, and physical performance) but also the outcomes of blood biomarkers (including inflammatory factors, hormones, growth factors, and muscular injury biomarkers) and quality of life. For the measurement of muscle strength, we measured both upper and lower limb muscle strength. In previous studies, only upper limb muscle strength (Chang et al., 2018; Miller et al., 2018) or lower limb muscle strength (Wei et al., 2016; Wei and Ng, 2018; Camacho-Cardenosa et al., 2019) was assessed. But studies have demonstrated that sarcopenia is associated with the decline of whole-body muscle, so it is not enough to only study upper/lower muscle strength (Cruz-Jentoft and Sayer, 2019). Therefore, our study evaluated both upper and lower limb muscle strength for the included subjects. For the measurement of blood biomarkers, our study explored the effects of different training methods on the physiological mechanism of the progression of sarcopenia. However, there is a lack of studies focusing on the change in the blood biomarker level in older people with sarcopenia using VT. Thus, we speculated that VT can also improve the blood biomarkers related to sarcopenia so as to prevent and/or delay sarcopenia in older people. In addition, we aimed to explore the mechanism of sarcopenia by exploring the changes of the blood biomarker level caused by VT and RT in the subjects.

Our study also has a limitation: in the VT group, we reduced each vibration exposure time and increased the number of vibration repetitions. A study found that longer time at each vibration increases muscle fatigue of the subjects and decreases subjects' compliance (Silva-Grigoletto et al., 2011). Therefore, we reduced the vibration exposure time of each vibration and increased the number of vibration repetitions. But we are not sure whether this will also lead to muscle fatigue in older people with sarcopenia. Hence, in future experiments, we will increase the monitoring of subjects' movements and make timely adjustments.

